## 2. LIST OF ABBREVIATIONS AND DEFINITIONS

|             |                                                                            |
|-------------|----------------------------------------------------------------------------|
| 6-MWT       | 6-Minute Walk Test                                                         |
| AE          | adverse event                                                              |
| CGI-S       | Clinical Global Impression of Severity                                     |
| CHOP-Intend | Children's Hospital of Philadelphia Infant Test of Neuromuscular Disorders |
| CRF         | case report form                                                           |
| CRO         | contract research organization                                             |
| DMT         | disease modifying therapy                                                  |
| ECG         | electrocardiogram                                                          |
| EDC         | electronic data capture                                                    |
| EOS         | end of study                                                               |
| FVC         | Forced Vital Capacity                                                      |
| FPFV        | first patient first visit                                                  |
| FU          | follow up                                                                  |
| GPP         | Good Pharmacoevidence Practice                                             |
| HINE        | Hammersmith Infant Neurological Examination                                |
| HFMSE       | Hammersmith Functional Motor Scale Expanded                                |
| ICF         | informed consent form                                                      |
| ICH         | International Council for Harmonisation                                    |
| IDMC        | independent data monitoring committee                                      |
| IEC         | independent ethic committee                                                |
| IPPV        | intermittent positive-pressure ventilation                                 |
| NIV         | non-invasive ventilation                                                   |
| NMD         | neuromuscular disease                                                      |
| NMPA        | National Medical Products Administration                                   |
| NSAE        | Nonserious adverse event                                                   |
| PRO         | patient-reported outcomes                                                  |
| QC          | quality control                                                            |
| RULM        | Revised Upper Limb Module                                                  |
| SAE         | serious adverse event                                                      |
| SAP         | statistical analysis plan                                                  |
| SAS         | statistical analysis system                                                |
| SMA         | spinal muscular atrophy                                                    |
| SMN         | survival motor neuron                                                      |
| TGI         | Total Global Impression                                                    |
| WHO         | World Health Organization                                                  |

CONFIDENTIAL

### 3. INTRODUCTION

#### 3.1. Study Rationale

Due to the improvements in treatment and technological advances, the natural history of SMA patients has changed. Especially in rare diseases a comprehensive and systematic collection of data regarding the natural history of the disease and the influence of different drug treatments is crucial to improve the care of these patients. So far, current clinical trials regarding new therapeutic approaches for SMA patients only cover a subgroup of the broad spectrum of severity of SMA. Thus, there are strong unmet needs to monitor all treated and untreated SMA patients and particularly in China, given the relatively large number of underserved Chinese patients. The registry will facilitate the understanding of disease progression and treatment effectiveness for Chinese pediatric patients diagnosed with SMA.

The aim of this registry is to both retrospectively collect and prospectively monitor pediatric SMA patients in the long term to achieve a better understanding of the natural history and outcomes of patients. The planned SMA registry will provide an online platform to collect longitudinal data on pediatric SMA patients. As a disease-specific system, the database will collect data from all available pediatric SMA patients independent of their actual treatment regimen. Items for data collection are aligned with TREAT-NMD.

#### 3.2. Background

##### 3.2.1. Overview of Disease

Spinal muscular atrophy (SMA) is a neuromuscular disorder that is primarily characterized by degeneration of the anterior horn cells of the spinal cord resulting in muscle atrophy and muscle weakness. It is an autosomal-recessive disorder caused by a homozygous deletion or mutation in the survival motor neuron 1 (SMN1) gene on chromosome 5q13. With an incidence of 1:6,000 to 1:10,000, SMA is among the rare diseases. The severity of the disease is highly variable and correlates with the age of onset. SMA is classified into four different subtypes (Table 2).

Table 2: Classification of different phenotypes of SMA

| Type | Age of onset
(% of SMA patients) | Best motor function  | Life expectancy with a natural course of disease | Clinical features                                                                                                               |
|------|-------------------------------------|----------------------|--------------------------------------------------|---------------------------------------------------------------------------------------------------------------------------------|
| 1    | 1-6 months
(50-60%)              | Never sits           | < 2 years                                        | Muscle weakness, floppy infant, weak cough, difficulties in swallowing, areflexia, tongue fasciculations, paradoxical breathing |
| 2    | 7-18 months
(30%)                | Sits but never walks | > 2 years                                        | Delay in motor development, muscle weakness, fine tremor in upper extremities, weak cough, scoliosis, joint contractions        |

CONFIDENTIAL

The information contained herein may not be used, disclosed, or published without the written consent of Biogen

|   |                      |       |           |                                                                                      |
|---|----------------------|-------|-----------|--------------------------------------------------------------------------------------|
| 3 | > 18 months
(10%) | Walks | Adulthood | Variable muscle weakness, scoliosis, joint contractions, loss of the ability to walk |
| 4 | 10-30 years
(1%)  | Walks | Adulthood | Variable but mild muscle weakness                                                    |

### 3.2.2. Available Therapies for Disease

Disease management is mainly based on a multidisciplinary management to improve motor, respiratory, gastrointestinal, and orthopedic symptoms. With technical advancements and thus the possibility to provide non-invasive ventilator support and enteral feeding to the affected patients, survival has increased. In 2017, a consensus statement for standards of care in SMA was published, nonetheless, there is high variability in the standards of care for patients with SMA.

Current therapeutic strategies include mainly respiratory, feeding and orthopedic management and supportive pharmacologic therapy. These therapies improve muscular function, quality of life and longevity, but do not directly target the disease mechanism. Presently in China, there is one registered and approved therapy to treat 5q-SMA patients (nusinersen). This compound is an antisense oligonucleotide targeting the splicing of exon 7 of the SMN2 gene, aiming at increasing the production of a full-length SMN protein. This compound is administered through intrathecal administration, with 4 loading doses over 63 days, followed by maintenance doses every 4 months. New therapeutic compounds, gene therapy (AVXS-101, Avexis) was approved by FDA and EMA recently. Small molecule targeting the splicing of SMN2 was also approved by FDA and EMA.

Based upon a better understanding of the molecular genetics of SMA, there has been a promising approach for the development of novel drugs intervening with the pathophysiology of SMA. Nusinersen is the first drug that has been approved for the treatment of 5q-SMA. It was approved in the United States in December 2016, in Europe in June 2017, and in China in February 2019.

### 3.3. Benefit-Risk Assessment

The study results on natural history and treatment patterns will provide better understanding of SMA prognosis and effective treatment interventions. The study will only observe regular clinical practice, and therefore, no additional health risks will be imposed on participants other than the existing risks present with the treatment or the disease.

The potential privacy risks to health data related to participation in this study are justified by the anticipated benefit to advance medical knowledge.

For patients on DMTs, detailed information about the known and expected benefits and risks and reasonably expected adverse events (AEs) of those DMTs is available in their respective Investigator's Brochure(s) or Prescribing Information.

CONFIDENTIAL

#### 4. STUDY OBJECTIVES AND ENDPOINTS

The objective of this registry is to longitudinally follow up pediatric patients (aged <18) with 5q-SMA to obtain information on both the natural history of the disease (from patients who received supportive care only) and the effectiveness and safety of disease modifying therapies (DMT), nusinersen in particular. Disease characteristics, treatment patterns, and outcomes (please refer to the section of outcome measurements) will be collected by extracting relevant information from medical records. Since this is not an experimental study, treatment plans will not be altered by participation, and all clinical managements including supportive care, DMTs, and concomitant medications will be administered based on healthcare providers' clinical judgements without stakeholders' interventions.

Currently, three DMT drugs are available including nusinersen, onasemnogene abeparvovec, and risdiplam in the US, but only nusinersen is approved by the National Medical Products Administration (NMPA) in China. In line with the main objective of this registry, and in case there will be more NMPA-approval DMTs in the future, in addition to nusinersen, this registry will also collect information on other DMTs once they become available in China.

| Primary Objective                                                                                    | Primary Endpoints                                                                                                                                                                                                                       |
|------------------------------------------------------------------------------------------------------|-----------------------------------------------------------------------------------------------------------------------------------------------------------------------------------------------------------------------------------------|
| To describe the natural history and utilization of DMT among pediatric Chinese patients with 5q-SMA. | Not applicable.                                                                                                                                                                                                                         |
| Additional Objectives                                                                                | Additional Endpoints                                                                                                                                                                                                                    |
| To describe the effectiveness of DMT.                                                                | Time to mortality, motor function, motor measures, pulmonary function, scoliosis, hospitalizations and comorbidities, clinical observations, patient reported outcomes, wheelchair use, nutrition and electrophysiology and biomarkers. |
| To evaluate the safety of DMT.                                                                       | Adverse events and serious adverse events.                                                                                                                                                                                              |

CONFIDENTIAL

## **5. STUDY DESIGN**

### **5.1. Study Overview**

This is a prospective, multicenter, non-randomized registry for treated and untreated pediatric patients with SMA in a real-world setting. Data obtained within regular patient visits prior to registry inclusion may be documented retrospectively. The study plans to recruit approximately 600 pediatric patients from 20-25 sites in China.

The current aim of this registry is to include centers in China meeting the structural and personnel requirements for performing the planned regular registry-related investigations. These reference centers in China will be selected from COEs which 1) have already been well trained on motor function evaluation, 2) have the potential to enroll and follow reasonable patient numbers, 3) have experience in treating SMA with nusinersen, and 4) have experience in conducting clinical trials. The participation of these centers in the data collection for this study will improve cooperation and harmonization between pediatric care centers for patients with spinal muscular atrophy.

See Figure 1 for a schematic of the study design.

### **5.2. Study Duration for Participants**

The study period will consist of identification and enrollment of participants meeting the eligibility criteria, observation of their treatment, and their follow-up. The total duration of study participation for each participant will be up to 60 months.

### **5.3. Study Stopping Rules**

The Sponsor may terminate this study at any time, after informing the Investigators. The Sponsor will notify the Investigators and its partner (if appropriate) when the study is to be placed on hold, completed, or terminated.

### **5.4. End of Study**

The end of study is last participant, last visit, for final collection of data.

CONFIDENTIAL

## **6. STUDY POPULATION**

Subjects will be included in the registry, following diagnosis, as long as all inclusion criteria and no exclusion criteria are fulfilled.

### **6.1. Inclusion Criteria**

To be eligible to participate in this study, candidates must meet the following eligibility criteria at Day 0, or at the time point specified in the individual eligibility criterion listed:

1. Ability of the participant and/or his/her legally authorized representative (e.g., parent or legal guardian), as appropriate and applicable, to understand the purpose and risks of the study, to provide informed consent, and to authorize the use of confidential health information in accordance with national and local privacy regulations.
2. Genetically confirmed 5q-SMA.
3. Age < 18 years at enrollment.

### **6.2. Exclusion Criteria**

Candidates will be excluded from study entry if any of the following exclusion criteria exist at Day 0, or at the time point specified in the individual criterion listed:

1. Unable or unwilling to provide informed consent.
2. Other types of SMA (non 5q-SMA).

### **6.3. Screening**

Once informed consent is obtained, a unique identification number is assigned that will be used on study-related documents pertaining to the participant. Any identification numbers that are assigned will not be reused even if the participant does not continue in the study. Study sites are required to document all screened participants initially considered for inclusion in the study.

CONFIDENTIAL

## **7. STUDY TREATMENT**

### **7.1. Study Treatment Management and Administration**

As a disease registry, there is no study treatment. No DMT will be supplied by The Sponsor for this study. Any DMT must be administered according to standard local prescribing procedures or the instructions in the approved Prescribing Information.

### **7.2. Concomitant Therapy**

Prescribed concomitant medications and therapies including physiotherapy will be recorded from the index date. Concomitant medications and therapies used together with any reported AEs or SAEs during the same period also need to be documented. The required details of documentation include drug or therapy name and dosage (amount, frequency, duration).

Concomitant medications and therapies will be listed in the eCRF.

CONFIDENTIAL

## **8. WITHDRAWAL OF PATIENTS FROM THE STUDY**

The registry patient can have his/her participation in the registry terminated prematurely at any time, without having to give reasons. Patients must be withdrawn from the study for any one of the following reasons:

- The participant withdraws consent.
- The participant is unwilling or unable to comply with the protocol.
- The physician withdraws the participant from the study for medical reasons.

The treating physician has the right to terminate registry participation of a patient according to the following conditions:

- Loss of contact.
- Logistical reasons (patient changes his/her doctor or hospital or moves to another location).
- Extreme circumstances arise which make any registry-relevant follow-up impossible.

The reason for the participant's withdrawal from the study must be recorded in the participant's case report form (CRF).

The investigator has the right to terminate the registry at one of the centers. The registry can be terminated prematurely at his center by the investigator if, for instance, unforeseeable circumstances have arisen at the trial center which preclude the continuation of the registry or the investigator considers that the resources for continuation are no longer available. The sponsor can initiate the exclusion of a center from further participation if, serious problems arise with regard to the quality of the collected data which cannot be resolved. Premature termination at one of the trial centers does not automatically mean a termination of the registry for already enrolled registry patients. The documentation of already enrolled registry patients will be reviewed for completeness and plausibility. Queries may be raised for further clarification before the center is closed. These queries must be answered properly by the center.

The sponsor/coordinating investigator is under obligation to monitor the progress of the registry about intended developments and, if necessary, initiate the termination of the entire registry. The sponsor/coordinating investigator will be supported in this responsibility by the contract research organization, if necessary. Further, the coordinating investigator can prematurely terminate the registry if sufficient financial funding is not available anymore. All published data will be stored and archived for 10 years.

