| Study Indication:               | Spinal Muscular Atrophy (SMA)                                                                                                                                                                                                                                                                                                                                                                                                                                                                                                                                                                                                                                                                                                                                                                                                             |
| Study Rationale:                | 
The planned registry project will provide a platform to collect longitudinal clinical routine data on Chinese SMA patients. Items for data collection will be aligned with TREAT-NMD. SMA has a broad spectrum of severity and clinical trials only cover a subgroup of these. Therefore there is a strong need to monitor the clinical status of all treated and untreated SMA in China. The registry will facilitate the understanding of disease progression and treatment effectiveness for Chinese pediatric patients diagnosed with SMA.
                                                                                                                                                                                                                                                                                     |

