This registry study will include both retrospective and prospective data collection. Eligible SMA patients will be recruited during the 24-month recruitment period and will be prospectively followed up to the end of study or deaths or willing to drop out, whichever comes first. If patients received DMT (including nusinersen and other DMTs) prior to the recruitment initiation and post April 28th, 2019 (as the date the first DMT, nusinersen, was launched in Chinese market), data will be retrospectively collected via medical chart review. Retrospective data collection will be considered complete for a participating patient if data of last available medical chart or latest survival status before recruitment initiation have been recorded in the electronic case report form (eCRF). Otherwise, patients will be prospectively followed up to the end of study or deaths or willing to drop-out, whichever comes first, after signing the ICF. For the DMTs treated group, the date of patients initiating DMT will be defined as the index date. For patients not receiving DMTs, the date of enrollment into the registry will be the index date. Baseline data will be collected within 30 days prior to the index date. Diagram of data collection is provided in Figure 1.

Since this is a non-interventional study and does not impose a visit schedule, patients will be treated according to physician's decisions. Only data that are available during routine visits will be documented. Recommended data collection schedules are set up to reflect the most likely patterns of routine clinical care of patients with and without DMT. To ensure the excellent level of compliance on data collection, schedule points are set to follow clinical routine visits, most likely happen on day 0, 14, 28, 63 then every 4 months for patients treated with nusinersen, and at day 0, 90 (in children with SMA type 1 < 2 years of age), 180 then every 6 months for untreated patients or those on other DMT. Retrospective data will be extracted according to the schedule as well.

CONFIDENTIAL

All data collected within the registry will be entered to the registry-specific e-forms by the responsible investigator, or a designated person, as timely as possible. Data entry and data corrections on e-forms are automatically tracked in the audit trail created by the EDC system. The EDC system and related IT infrastructure of this project will be based inside China.

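### Section 8 makes withdrawal mandatory on grounds that Section 9 does not list, and no general vital-status follow-up is stated afterwards, so survival may be biased upward

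*Protocol*

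**What the plan says.** Protocol Section 8 introduces its first list with "Patients must be withdrawn from the study for any one of the following reasons". Besides withdrawal of consent, the list contains "The participant is unwilling or unable to comply with the protocol" and "The physician withdraws the participant from the study for medical reasons". No criterion for medical reasons or for inability is given. A second list sets out when the treating physician has a right, not a duty, to end participation. It includes "Logistical reasons (patient changes his/her doctor or hospital or moves to another location", with no exception for a move to another participating centre.

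Other parts of the protocol describe a study with little for these rules to act on:

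- Section 7.1: "As a disease registry, there is no study treatment".
- Section 9: "Since this is a non-interventional study and does not impose a visit schedule". The notes to Table 1 in Section 1.3 add that no additional visits, tests or procedures are required.
- Section 9 also says that recruited patients "will be prospectively followed up to the end of study or deaths or willing to drop out, whichever comes first". Physician withdrawal and inability to comply are not among these end points.
- The Synopsis gives as rationale that "there is a strong need to monitor the clinical status of all treated and untreated SMA in China".

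Time to mortality is an additional endpoint (Section 4). Time-to-event endpoints are estimated by Kaplan-Meier (Section 11.3), over participation of up to 60 months (Section 5.2).

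**The concern.** In a treatment trial, withdrawal for medical reasons or non-compliance normally has something to stop: a study drug or a burdensome visit plan. This registry has neither. What ends on withdrawal is outcome collection. A site reading Section 8 and a site reading Section 9 could therefore handle the same child differently.

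The statistical stake is the censoring assumption. Kaplan-Meier estimates survival correctly only if children who are censored have the same later risk of death as those who stay. A withdrawal labelled medical can plausibly depend on prognosis, and because the term is undefined, sites may apply it unevenly. Section 9 asks for consecutive inclusion to limit selection at entry; Section 8 leaves room for selection at exit. Deaths are to be expected: Table 2 in Section 3.2.1 gives a natural life expectancy below two years for type 1. A statistical analysis plan can add sensitivity analyses, but it cannot restore deaths that the protocol stopped collecting.

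**Working it through.** **1. The two follow-up rules side by side**

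| Situation | Section 8 | Section 9 |
|---|---|---|
| Consent withdrawn or unwilling to continue | must be withdrawn | follow-up ends (voluntary drop-out) |
| Unable to comply | must be withdrawn | not an end point |
| Physician withdraws for medical reasons | must be withdrawn | not an end point |
| Change of doctor or hospital | physician may terminate | not an end point |

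The first row agrees; the other three do not.

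**2. What is collected after withdrawal**

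Section 10.3.2 has the investigator follow a serious adverse event that is ongoing at discontinuation until it settles. Events that start after withdrawal are reported to the sponsor only if judged related to nusinersen, so a later death from disease progression need not be captured. Section 10.1.2 defines serious adverse events for patients given a pharmaceutical product, and Section 9 ties safety data to patients on treatment. Cover for untreated children, who supply the natural-history data, is therefore unclear. No general collection of vital status after withdrawal is stated.

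**3. Size of a possible bias (illustration only)**

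The protocol states no mortality, withdrawal rate or event count, so there is no figure of its own to reproduce. Inputs:

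- S, the true 60-month survival: assumed 0.50, 0.80 or 0.90.
- q, the fraction of children who would die but are withdrawn shortly before death with the death not captured: assumed 10%, 25% or 50%.
- N = 600 (Section 11.5) and 60 months (Section 5.2).

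If q does not depend on time, the observed death hazard is (1 − q) times the true one, and Kaplan-Meier converges to

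S_obs = S^(1 − q).

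| True S | q = 10% | q = 25% | q = 50% |
|---|---|---|---|
| 0.50 | 0.50^0.90 = 0.536 | 0.50^0.75 = 0.595 | 0.50^0.50 = 0.707 |
| 0.80 | 0.80^0.90 = 0.818 | 0.80^0.75 = 0.846 | 0.80^0.50 = 0.894 |
| 0.90 | 0.90^0.90 = 0.910 | 0.90^0.75 = 0.924 | 0.90^0.50 = 0.949 |

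A simulation (600 children, exponential death times, withdrawal 0 to 3 months before death, 400 runs) gave 0.537, 0.592 and 0.706 for the first row, 0.818, 0.846 and 0.894 for the second, and 0.909, 0.924 and 0.948 for the third. The sampling standard deviation was between 0.010 and 0.022. With q = 0, meaning vital status is kept for every withdrawn child, the simulation returned 0.500, 0.799 and 0.900.

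To put q in numbers of children: at S = 0.80 with all 600 followed for 60 months, 600 × 0.20 = 120 would die, so q = 10%, 25% and 50% correspond to 12, 30 and 60 children.

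**The case against.** A reader might infer that the protocol forces the sickest children out of the registry. The text does not say that. The medical ground is circular: it applies only once a physician has chosen to withdraw the child, so no clinical state triggers it, and nothing links it to severity. The compliance ground has little to act on, because a child too ill for a test breaches no requirement. The logistical clause is a permission. The patient number serves throughout participation, and nothing forbids a transfer between sites, although none is described. All of this stands, and it limits the claim to what the rules allow rather than what they compel.

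There are also mitigations. Serious adverse events ongoing at discontinuation are followed; hospitalisation and life-threatening events count as serious (Section 10.1.2), and death is treated as the outcome of such an event (Section 10.3.2.1). Some deaths soon after withdrawal would thus be seen. If a fraction c of the otherwise missed deaths is captured and used in the analysis, q becomes q(1 − c): with c = 50%, q = 50% acts like 0.50 × (1 − 0.50) = 25%. The withdrawal reason must also be recorded, which supports sensitivity analyses in an analysis plan not available here. These points reduce the possible bias. They do not remove it: a recorded reason shows who left, not who later died.

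Finally, S and q are assumed, and time to mortality is one of many additional, descriptive endpoints; no primary endpoint is defined. That stands, and it limits the weight of the figures.

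**Conclusion.** Sections 8 and 9 give sites different rules for ending follow-up, and two of the mandatory grounds in Section 8 fit poorly with a registry that has no treatment and imposes no visits. Because no general vital-status follow-up after withdrawal is stated, censoring of time to mortality may be informative, and the likely direction is overstated survival.

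The size is unknown. Under the assumed values, a true 80% survival is overstated by about 2, 5 or 9 percentage points (81.8, 84.6 and 89.4 minus 80). At 90% survival and q = 10% the error is about 1 point, no larger than sampling error; at 50% survival and q = 50% it is about 21 points. These figures rest on withdrawal shortly before death, a constant q and no later capture of the deaths. A larger registry would not cure such a bias.

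A reader might also infer that motor function is overstated, or that treated and untreated children are affected equally. The calculation covers survival only, and the protocol supports neither statement. The point deserves correction because outcomes not collected cannot be recovered at analysis, but it does not show that the registry's results will be materially wrong.

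**What to change.** - Make Section 8 agree with Section 9. Keep withdrawal of consent, or unwillingness to continue, as the ground that ends data collection, and remove medical reasons and inability to comply as mandatory grounds for it.
- For other patients who stop attending, record vital status (alive or dead, with date) up to data cut-off, where consent allows.
- State that a child who moves to another participating site continues under the same patient number. Section 9 already makes that number the identifier throughout participation and plans a check against duplicate entries.

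Continued chart abstraction for every withdrawn patient is not proposed: it would reach unwilling families and hospitals outside the registry.

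The cost is protocol wording, a small eCRF item and some site effort for vital-status contacts. The contact attempts in Section 8.1 are a starting point, but they concern patients who miss visits and cannot be reached, so the added effort is not zero. No treatment or clinical rule changes.
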